#### Participants and recruitment

Females presenting to ED within three days of injury with suspected concussion are recruited by ED healthcare professionals. Participants are invited to participate if they are biologically female (self-report), of reproductive age (16–50 years) and have a confirmed diagnosis of concussion from the consulting healthcare professional. The diagnostic criteria for concussion are those outlined in the most recent international consensus statement from the concussion in sport group. [51] Participants will be excluded if they have Polycystic Ovarian Syndrome (PCOS), a pre-diagnosed psychiatric disorder or neurological condition (e.g. epilepsy, cerebral palsy) or if they have had more than three previously diagnosed concussions; these are known modifiers for prolonged recovery. [52, 53] These specific exclusion criteria will be ascertained by the consulting ED healthcare professional as part of the initial routine assessment for concussion. Full inclusion/exclusion criteria are shown in Table 1. The standard concussion assessment is detailed in Fig. 1. Study recruitment commenced February 2022, however there was interruption due to COVID related sickness and changes in the ED through November 2022. The study recommenced in January 2023 and is in progress.

**Table 1 Tab1:** Inclusion and exclusion criteria

Inclusion criteria	Exclusion criteria
Females of reproductive age: 16–50 years (with a menstrual cycle for a minimum of 2 years if naturally cycling)	Had three or more previously diagnosed concussions
Natural regular menstrual cycle 28–35 days long, or Currently taking Oral Contraceptive Pill (OCP), or Currently have Intra Uterine Device (IUD), or	Current concussion was more than 3 days ago
	Post-menopause
	Started taking medication that would alter reproductive hormone concentrations (Corticosteroids, e.g., Prednisone. Antidepressant or Antipsychotic medication) within the last 3 months
	Current clinical diagnosis of an eating disorder
	Pre-diagnosed psychiatric disorder
	Pre-diagnosed neurological condition
	Polycystic Ovarian Syndrome (PCOS)
	Oligomenorrheic (irregular periods), or
	Amenorrheic (loss of periods for 3 months or longer)
Confirmed diagnosis of concussion by a medical doctor (within 3 days of injury)	GCS^a^ score less than 15 at 4 h after initial assessment. These patients may be referred for a CT scan and will not be eligible for the study

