#### Sample size calculation

Using PASS15 software, and a Cox Proportional-Hazards regression model it was estimated that the number of participants needed to examine the primary aim (recovery time in days) is 30. This will allow the detection a hazard ratio of 1.5 (log hazard ratio coefficient = 0.4055), with 80% power, and a type I error rate of 0.05. This was calculated assuming a covariate SD of 1.5, a multiple regression R^2^ (variable of interest regressed on covariates) of 0.2, and an expected event (clinical recovery) rate of 0.9 within the follow-up period. [16, 22] Allowing for 20% drop out during follow-up, 38 participants will be recruited. As of 18 August 2023, 14 eligible women have started the study.

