#### Surveys and questions

Survey and question data are collected and managed using REDCap (Research Electronic Data Capture) which is a secure, web-based software platform designed to support data capture for research studies. [56, 57] Participants are provided with an online link to REDCap via email. A new link is sent every seven days after initial appointment until a full return to work/study is reported. It takes approximately 10 min to complete all questions each week.

Two concussion specific questions are asked only once, seven days after the initial appointment. The first question relates to concussion history and is utilised to capture the number of previous concussions the participant has had. This information is important as prior concussion can impact recovery from subsequent concussions. [52] The second question is used to capture whether the participant’s concussion is sport related or not.

Participants are also asked to complete the Low Energy Availability in Females Questionnaire (LEAF–Q) online seven days after initial assessment and then at seven-day time intervals throughout recovery. The LEAF-Q [58] is designed and validated to evaluate physiological symptoms of insufficient energy intake or low energy availability (LEA). The LEAF-Q contains questions regarding injuries, gastrointestinal and reproductive function. In Sect. 3.2 three questions (19 items) relate to menstrual function including recent menstrual history. This questionnaire section is used to determine hormonal profile of participants and has been modified as outlined below.

Part C of Sect. 3.2 includes the following question:C: Do you have normal menstruation? Yes ☐ No (go to question C6) I don’t know (go to question C6)C1: If yes, when was your last period? 0–4 weeks ago ☐ 1–2 months ago ☐ 3–4 months ago ☐ 5 months ago or more ☐

This question has been modified to capture more accurate detail about the last menstrual cycle as follows:C: Do you have normal menstruation? Yes ☐ No (go to question C6) I don’t know (go to question C6)C1: If yes, when was your last period? 1 week ago ☐ 2 weeks ago ☐ 3 weeks ago ☐ 4 weeks ago ☐ 1–2 months ago ☐ 3–4 months ago ☐ 5 months ago or more

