Participants are categorised into one of five hormone profiles as follows; 1) Follicular phase if question C1 is answered as “1 week ago”, 2) Mid-cycle if question C1 is answered “2 weeks ago”, 3) Luteal phase if question C1 is answered “3 weeks ago” or “4 weeks ago”, 4) Oligomenorrheic if C1 was answered “1–2 months ago”, “3–4 months ago” or “5 months ago or more”, 5) Using contraceptive if question 3.1a is answered “yes”.

Scoring of question 3.2 remains the same, i.e., if a participant ticks any of the boxes within the 0–4 weeks’ timeframe the same score is applied as the original question. In eumenorrheic participants this will help estimate menstrual cycle phase at point of injury. This information is used to understand any association between hormonal profile and or LEAF_Q score with symptom severity and duration of concussion.

The Brain Injury Screening Tool (BIST) is a brief screening tool for use on initial presentation after injury to guide health care pathway decision making and to monitor symptoms and recovery over time. [59] The BIST was developed in the NZ context to fit the clinical environment and to provide consistency across multiple environments and referral pathways (e.g. GP clinic, ED, Urgent Care Centres), the tool has also been psychometrically tested. There are two sections in the BIST; the first section is used to determine if there are any clinical ‘red flags’ which require referral to hospital, therefore this component is not included in this study. The second section of the BIST includes a 16-item symptom report scale for patients to rate how much they now experience the symptoms listed on a scale of 0 (not at all) to 10 (severe). Higher symptom scores are indicative of higher symptom burden. Participants are asked to complete this part of the BIST at point of presentation with injury and at seven-day time intervals throughout the study to monitor symptoms and recovery over time.

The final question asks if the participant has made a full return to work/study and how many follow-up appointments they had. The number of days between injury and full return to work/study will be used as a proxy for recovery. This question is included in the weblink sent at all timepoints (i.e., 7, 14, 21, 28 days etc.) until the participant reports they have achieved a full return to work/study, at which point participation in the study will be complete. Detail of information collected each week is included in Table 2.

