**Table 2 Tab2:** Research measures and collection points

Measure	How	Who	When		
			Initial assessment	During recovery (7-day time intervals)	Full return to work/study
Saliva Samples	Passive drool into cryovial	Consulting clinician, research assistant or Lead Researcher	X		
Number of prior concussions^b^	Online^a^	Participant to complete		X	
Sport or non-sport related concussion^b^	Online^a^	Participant to complete		X	
LEAF-Q	Online^a^	Participant to complete		X	
BIST	Online^a^	Participant to complete	X	X	
Number of days from injury to recovery (full return to work/study)	Online^a^	Participant to complete			X

^a^Weblink emailed to participant

^b^Question only asked once, at first (7-day) timepoint

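### The primary event, full return to work or study, is undefined for eligible women who are in neither, and no rule or status item covers them

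*Protocol article*

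**What the plan says.** **Event.** Under Surveys and questions: "The number of days between injury and full return to work/study will be used as a proxy for recovery". Table 2 likewise treats recovery and full return to work or study as the same thing. No second recovery criterion is given, although Brain Injury Screening Tool (BIST) symptoms are collected weekly.

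**End of follow-up.** The same event closes follow-up: "A new link is sent every seven days after initial appointment until a full return to work/study is reported". The question is repeated "until the participant reports they have achieved a full return to work/study, at which point participation in the study will be complete". No maximum duration is stated.

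**Eligibility.** Participants and recruitment says "Full inclusion/exclusion criteria are shown in Table 1". That table begins with "Females of reproductive age: 16–50 years" and has no item on employment or study. The text after Fig. 1 says that patients injured through interpersonal violence, assault or motor vehicle accidents should be included.

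**Measures.** Table 2 lists saliva, prior concussions, whether the concussion was sport related, LEAF-Q, BIST and days to recovery. It has no work or study status.

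**Analysis and sample size.** Aim 1 is a Cox regression of days to recovery on hormone profile (five profiles). The sample size assumes an "expected event (clinical recovery) rate of 0.9 within the follow-up period".

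**Limitations.** The article concedes that going back to work need not mean full physiological recovery. It does not mention women who have no work or study.

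**The concern.** The entry criteria admit women for whom the primary event cannot be observed in a meaningful way: unemployed women, full-time carers, students between terms. The article gives no rule for them. Their recorded time would depend on how each one reads the question:

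- If she never reports a return, weekly links continue with no stated end, and she is carried in the risk set as not yet recovered until last contact.
- If she says at the first survey that nothing is keeping her from work, she is recorded as recovered by day 7.

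Neither time measures recovery. On the measures listed, these women could not be identified afterwards, so an analysis plan written later could not separate them. The sample is small: 38 women over five profiles is 38/5 = 7.6 per profile, so a few such times could matter if they fell in one profile. Events are lost as well if these women never have one.

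**Working it through.** **1. Reproduce the plan's sample size.** Inputs from Sample size calculation: hazard ratio 1.5 (log 0.4055), 80% power, type I error 0.05 (two-sided reproduces the figure), covariate SD 1.5, R² 0.2, event rate 0.9, dropout 20%.

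Events needed: D = (z₀.₉₇₅ + z₀.₈₀)² / [SD² × (log HR)² × (1 − R²)] = (1.960 + 0.842)² / (2.25 × 0.1644 × 0.8) = 26.52.

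N = 26.52 / 0.9 = 29.5, so 30. Recruited: 30 / 0.8 = 37.5, so 38. Both stated figures reproduce. The 0.9 is labelled clinical recovery, which is not literally the event analysed.

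**2. Loss of events.** Let f be the share of women who cannot have the event. The documents do not give f; 10% and 20% are assumptions. This step uses the literal reading, in which these women never report a return.

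Event rate = 0.9 × (1 − f). Power at N = 30 is Φ(√(30 × rate × 0.8) × 1.5 × 0.4055 − 1.960).

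| f | Event rate | Events at N = 30 | Power at N = 30 | N needed | Recruit (N / 0.8) |
|---|---|---|---|---|---|
| 0 | 0.90 | 27.0 | 80.7% | 30 | 38 |
| 10% | 0.81 | 24.3 | 76.5% | 33 | 42 |
| 20% | 0.72 | 21.6 | 71.5% | 37 | 47 |

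**3. Distortion of the profile comparison.** Simulated cohorts with no true difference compared one profile of 8 women with the other 30. Recovery times were exponential with a 14-day median, cut at 12 weeks (both assumed). The result is the median estimated hazard ratio for the profile of 8.

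| Affected women | How they are recorded | Median HR |
|---|---|---|
| None | – | 1.01 |
| 2 of 8, 0 of 30 | never recovered | 0.49 |
| 3 of 8, 0 of 30 | never recovered | 0.34 to 0.35 |
| 2 of 8, 4 of 30 (25% v 13%) | never recovered | 0.76 |
| 2 of 8, 7 of 30 (similar shares) | never recovered | 0.97 |
| 1 of 8, 4 of 30 (similar shares) | never recovered | 0.99 |
| 2 of 8, 0 of 30 | recovered at day 7 | 1.20 to 1.29 |
| 3 of 8, 0 of 30 | recovered at day 7 | about 1.4 |

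Where a range is shown, repeat runs differed slightly. With all affected women in one profile and recorded as never recovered, p < 0.05 occurred in 24% of runs with two women and about 63% with three, against 5% with none. With none, the 95% range of the estimated hazard ratio was already 0.45 to 2.42.

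The size therefore depends on imbalance between profiles, and the direction on how the women answer.

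**The case against.** The strongest reply is that the article fixes less than the point seems to need. It paraphrases the return question without its response options, and names Cox regression without coding or censoring rules. A not-applicable option may exist, a carer may count caring as work, or such women may be left out of Aim 1. Details of this kind are commonly left to a full protocol or analysis plan. The proxy is also openly described as imperfect, and BIST symptoms follow recovery separately.

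Part of this stands. A reader might infer that women without work or study are counted as unrecovered. No passage says so; that is only the literal reading, and an early yes would bias the comparison the other way.

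A reader might also take hazard ratios of 0.49 or 0.35 as the expected bias. They are a one-profile worst case, and 0.49 lies inside the ordinary noise for 8 women. Nothing in the documents links work or study status to hormone profile. Three of the five profiles are cycle phases at injury, with no evident reason to track employment; a link is more conceivable for the contraceptive profiles, but it is conjecture there too.

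The reply does not remove the gap. The event, the end of follow-up, the eligibility list and the measures table are all set out in the article, and together they admit women for whom the event has no meaning. An analysis plan cannot use a status that was not collected. The stated limitation concerns how well return to work reflects recovery, not women with nothing to return to.

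**Conclusion.** The point holds as a gap in the definition of the primary endpoint. The event is undefined for women in neither work nor study, the criteria admit them, and the listed measures do not identify them. Their recorded times would be unrelated to recovery, in a direction that the text does not settle.

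The cost in power is modest: about 4 to 9 percentage points at N = 30 (80.7% to 76.5% or 71.5%), if 10% to 20% of women are affected and never have the event. Bias between profiles ranges from almost none when these women are evenly spread to a hazard ratio further from 1 than the design's target of 1.5 when two or three fall in one profile and are recorded as never recovered (1/0.49 = 2.0; 1/0.35 = 2.9). The share affected, its spread over profiles, the 14-day median and the 12-week cut are all assumptions. The sample size arithmetic itself is not in error.

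**What to change.** 1. Record work and study status at injury for every participant. Ask women already enrolled retrospectively; 14 of the planned 38 had started by 18 August 2023.
2. Define the Aim 1 event as full return to pre-injury work or study or, for women with neither, to usual daily activities. Extend the existing weekly question to match.
3. Add a sensitivity analysis of Aim 1 restricted to women in work or study at injury.

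The cost is one added item, a reworded question and one further model. The downside is an endpoint that is slightly less uniform across participants, which the sensitivity analysis addresses.

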## Methods/design

### Aim

The aims of this study are to: 1) determine if the time to recovery (in days) differs among groups categorised by their hormone profiles at the point of concussion injury, 2) examine whether the ratio of sncRNAs in saliva differ across groups categorised by their hormone profiles at the point of concussion injury, 3) assess whether self-reported symptoms differ among groups categorised by their hormone profiles at the point of concussion injury, and 4) investigate whether low energy availability changes across the recovery period, and if this is associated with symptoms experienced.

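### Follow-up stops at the first reported full return, so failed returns go undetected and women returning by the first link give no within-woman LEAF-Q change for Aim 4

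*Protocol article*

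**What the plan says.** Under Surveys and questions, the Protocol article sets a weekly schedule: "A new link is sent every seven days after initial appointment until a full return to work/study is reported". The question on return to work or study is in every link "until the participant reports they have achieved a full return to work/study, at which point participation in the study will be complete". Procedures and measures states the same rule. Days from injury to this reported return serve as the proxy for recovery and are the Aim 1 outcome. The article gives no minimum duration of return, no confirming contact and no rule for a return that is reversed.

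The LEAF-Q is first completed seven days after the initial assessment and then weekly. Table 2 marks it only in the column for the 7-day intervals, neither at initial assessment nor at full return. The BIST is marked at initial assessment as well.

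Aim 4 is to "investigate whether low energy availability changes across the recovery period, and if this is associated with symptoms experienced". Data analysis specifies a linear mixed model for low energy availability with day of recovery, total symptom burden and their interaction as fixed effects, and participant as a random effect.

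**The concern.** Two consequences follow from the data collection rule, and a later analysis plan cannot undo either, because the data will not exist.

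**Aim 1.** A woman who reports full return, relapses after that survey and stops work again remains an event at her first date. Measured against sustained return, her time can only be too short. The study cannot say whether this happened to none of the women or to several.

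**Aim 4.** The number of LEAF-Q scores a woman gives is set by how long she takes to recover. A woman who reports return on the first link has at most one score, so nothing can be learned about change within her. Scores at later weeks come only from women who have not yet returned. The estimated course over days therefore describes mainly the slower recoverers, while the aim is worded for the recovery period of the whole cohort.

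**Working it through.** **1. The plan's own figure.** Inputs from Sample size calculation: log hazard ratio 0.4055, covariate SD 1.5, R² 0.2, event rate 0.9, 80% power, type I error 0.05 (two-sided assumed).

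- Events = (1.960 + 0.842)² / (1.5² × 0.4055² × (1 − 0.2)) = 26.5.
- Participants = 26.5 / 0.9 = 29.5, rounded up to 30.
- With 20% dropout: 30 / 0.8 = 37.5, rounded up to 38.

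Both stated numbers reproduce and are not in dispute. About 0.9 × 30 = 27 events carry Aim 1, so each misdated event is 1/27, or 3.7%, of the events. The article gives no rate of failed returns, so the size of this part stops there.

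**2. Share of women with a single LEAF-Q.** The article gives no median or distribution of recovery times, so both are assumed here. With time T counted from the initial appointment, the share is P(T ≤ 7):

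- exponential: 1 − 0.5^(7/m), where m is the median;
- Weibull, shape 2: 1 − 0.5^((7/m)²);
- lognormal, log-SD s: Φ(ln(7/m)/s).

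| Median (days) | Exponential | Weibull, shape 2 | Lognormal, s = 0.8 | Lognormal, s = 0.5 |
|---|---|---|---|---|
| 7 | 50% | 50% | 50% | 50% |
| 14 | 29% | 16% | 19% | 8% |
| 21 | 21% | 7% | 8% | 1% |
| 28 | 16% | 4% | 4% | 0.3% |

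The 50% at a 7-day median holds by construction. Under the exponential, the counts are 15, 9, 6 and 5 of the 30 women needed, or 19, 11, 8 and 6 of the 38 recruited. Presentation may be up to 3 days after injury, so the first link falls 7 to 10 days after injury.

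**3. Who supplies the within-woman trend.** With k weekly scores, a woman's within-person sum of squares for time, in weeks, is k(k² − 1)/12. This is zero for k = 1, 0.5 for k = 2 and 5 for k = 4. Simulating 400,000 recovery times per case over the same four medians, the slowest fifth of women hold these shares of the total:

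- exponential: 89% to 91%;
- Weibull, shape 2: 57% to 64%;
- lognormal, s = 0.5: 66% to 72%;
- lognormal, s = 0.8: 92% to 93%.

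The dominance of slow recoverers does not depend on the exponential assumption, although its degree does. Under the exponential, one extra score per woman (k + 1 in the formula) lowers the share to 75% to 88%.

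**4. What single-score women add to the mixed model.** In a random-intercept model the information on the day slope is the sum over women of X′V⁻¹X. It was evaluated for 30 women with 3, 9 or 15 of them giving a single day-7 score, the others giving 2 to 8 weekly scores, and an assumed intraclass correlation of 0.3 to 0.9. Including the single-score women lowers the standard error of the slope by 0.1% (3 women, correlation 0.9) to 5.5% (15 women, correlation 0.3: 0.0798 to 0.0754). That gain comes entirely from comparison between women.

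**The case against.** The protocol defines its event as a reported return, calls it a proxy, and concedes under Strengths and limitations that it need not reflect full physiological recovery. An early return is therefore wrong only against a different endpoint. This stands, and it is why the primary event should stay as defined. The conceded limitation does not, however, cover returns that fail.

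A reader might infer that the Aim 1 times, or the comparison between hormone profiles, are shown to be biased. The documents do not support that. No failure rate is given, and distortion of the comparison would need failed returns to differ between profiles. The question is also asked weekly, so a woman who goes back on day 2 and stops by day 6 can still answer no on day 7. Only a relapse after the reporting survey is lost.

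A reader might also infer that women who return by the first link contribute nothing to Aim 4. They contribute to the LEAF-Q/symptom association, which is half of the aim, and slightly to the day effect. By week 4 only unrecovered women are still in recovery, so a trend estimated in them is partly what the aim asks for. Total symptom burden, a likely correlate of stopping, is already in the model.

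Finally, the single score has two causes: the stopping rule and the absence of a LEAF-Q at initial assessment. A score taken after return also falls outside the recovery period as Aim 4 words it, and extra scores reduce the imbalance only in part. These points stand and shape the fix.

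**Conclusion.** The point holds in limited form, as an inexpensive improvement to data collection rather than a flaw that invalidates the primary analysis.

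- A return that fails after the reporting survey cannot be detected. The number of such returns is unknown and cannot be derived from the article.
- A woman who reports return on the first link gives at most one LEAF-Q and no within-woman change. The share of such women is 16% to 50% under exponential recovery with medians of 28 to 7 days. Under the other shapes tried it is 50% at 7 days, 8% to 19% at 14 days and 0.3% to 4% at 28 days. The exponential figures should not be read as the expected size.
- The later part of the Aim 4 trend is estimated mainly in slower recoverers under every shape tried.

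The calculated 30 and 38 are unaffected.

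**What to change.** 1. Keep the first reported full return as the primary event. Redefining it during recruitment would mix two definitions, because women already completed have no confirming contact.
2. In Surveys and questions and Table 2, add one automated link 7 days after the reported return, with the BIST, the LEAF-Q and a question on whether the woman is still at full work or study.
3. Use the answer for a sensitivity analysis of Aim 1 on sustained return, for example treating a woman who answers no as not yet recovered and censored at that contact. Report the number of failed returns and, separately, the number not answering, since women whose return failed may be less likely to reply.
4. Add the LEAF-Q at initial assessment, beside the BIST already taken there. Every woman who responds then has at least two scores. Fit the Aim 4 model with and without the score taken after return.
5. State in Data analysis that the Aim 4 day effect reflects mainly slower recoverers.

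**Cost.** By the article's figure of about 10 minutes for a full weekly set, the two additions take roughly 10 to 20 minutes per woman, plus an amendment, with no new visit and no change to the sample size. Some women will not answer. No extra data can be had from women already completed. By 18 August 2023, 14 women had started, so at that date 38 − 14 = 24 could still receive both additions, and any of the 14 still in follow-up could receive the extra link.

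### The items that define hormone profile are first collected at day 7, so naturally cycling women who never answer a weekly link are needlessly lost from Aim 2, and from Aim 3 where the day-0 BIST is used

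*Protocol article*

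**What the plan says.** The Aim section groups women in Aims 1 to 3 by hormone profile at the point of injury. Under Surveys and questions, the profile comes from the LEAF-Q. Of its menstrual section the article says: "This questionnaire section is used to determine hormonal profile of participants". Item C1 (last period) gives the cycle phase, and the contraceptive class is assigned by the rule "Using contraceptive if question 3.1a is answered" yes.

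The LEAF-Q is completed "online seven days after initial assessment and then at seven-day time intervals throughout recovery". The LEAF-Q row of Table 2 agrees: it is marked for the 7-day intervals and not for the initial assessment.

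Two outcomes are scheduled earlier. Table 2 marks saliva at the initial assessment. Participants are also asked to "complete this part of the BIST at point of presentation with injury and at seven-day time intervals throughout the study".

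Two further items, number of prior concussions and sport or non-sport injury, carry footnote b of Table 2: "Question only asked once, at first (7-day) timepoint". The text says the same: "Two concussion specific questions are asked only once, seven days after the initial appointment". Prior-concussion history is, however, also one of the exclusions checked in the ED: "These specific exclusion criteria will be ascertained by the consulting ED healthcare professional as part of the initial routine assessment for concussion".

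**The concern.** Hormone profile at injury is a day-0 exposure, and the miRNA ratio in the initial saliva sample is a day-0 outcome. Comparing the two needs no follow-up. Under the stated schedule a woman enters that comparison only if she answers an emailed survey at least a week later.

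A woman who gives saliva in the ED and answers no link has an outcome but no recorded cycle phase, so she cannot be placed in the Aim 2 ANOVA. The same holds for Aim 3 where the day-0 BIST is the outcome. Her sample would have been collected and stored to no purpose.

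The loss may also be selective. Women who already feel well, and women too symptomatic for a 10-minute survey, are both plausible non-responders, and symptoms are the Aim 3 outcome. This is a plausible mechanism; the article gives no data on it.

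**Working it through.** **The plan's own figures.** Sample size calculation gives HR 1.5, power 80%, alpha 0.05, covariate SD 1.5, R² 0.2 and event rate 0.9. For a Cox model, taking alpha as two-sided:

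- events = (1.960 + 0.842)² / [(ln 1.5)² × 1.5² × (1 − 0.2)] = 26.5
- N = 26.5 / 0.9 = 29.47, rounded up to 30
- with 20% drop-out: 30 / 0.8 = 37.5, rounded up to 38

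Both stated figures reproduce. The allowance is 0.20 × 38 = 7.6, about 8 women, which leaves 30 for Aim 1 (power 80.7%).

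**What a woman lost before day 7 contributes, by aim** (models from Data analysis):

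| Aim | Outcome in hand? | Would earlier grouping items rescue her? |
|---|---|---|
| 1, Cox on profile | No; return to work/study is first asked at day 7 | No; she has no follow-up time |
| 2, ANOVA of miRNA ratio | Yes; saliva at initial assessment | Yes |
| 3, ANOVA of symptoms | Yes, if she completed the first BIST | Yes, where the day-0 BIST is analysed |
| 4, mixed model of LEA | No; the LEAF-Q is itself the outcome | No; profile is not in this model |

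**Can her group be rebuilt from screening?** Table 1 requires a regular natural cycle, OCP or IUD, so the two contraceptive groups in Data analysis could be filled from the entry criteria. Those criteria do not give the date of the last period. The other three groups (follicular, mid-cycle, luteal) depend on C1 and cannot be rebuilt. The avoidable loss therefore falls on naturally cycling women.

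**Size.** The documents do not say how much drop-out occurs before day 7. I assume 2, 4 or 8 of the 38 (about 5%, 10%, or the whole 20% allowance). For a five-group ANOVA with equal groups and alpha 0.05, the noncentrality is N × f² with 4 and N − 5 degrees of freedom. The value f = 0.6 is also an assumption.

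| N analysed | N × 0.6² | Power at f = 0.6 | f detectable with 80% power |
|---|---|---|---|
| 38 | 13.68 | 80% | 0.60 |
| 36 | 12.96 | 77% | 0.62 |
| 34 | 12.24 | 74% | 0.64 |
| 30 | 10.80 | 66% | 0.69 |

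With equal groups there are 38 / 5 = 7.6 women per profile, so losing 4 is about half a group. If all losses fall on the three natural-cycle groups, the equal-group figures are only approximate.

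**The two one-off items.** As scheduled, a woman who skips the day-7 link but answers at day 14 has neither item. No model in Data analysis names them, so no stated analysis loses her for that reason.

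**The case against.** A reader might infer that a woman lost before day 7 leaves all four aims because of this schedule. The documents do not support that: Aims 1 and 4 lack their own outcomes for her, whenever the profile is asked. Nor should footnote b be read as applying to the LEAF-Q. It is attached only to the prior-concussion and sport rows, and the LEAF-Q repeats weekly, so a woman who misses day 7 but answers day 14 still supplies a C1 answer. Reminders, and whether a missed item is shown again, are operational details that an article may leave to the full protocol.

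Three further objections carry weight.

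- **The day-0 BIST may not exist.** Table 2 lists the BIST as completed through an emailed weblink, so a woman who ignores links may lack it. Data analysis also does not name the BIST timepoint for Aim 3. The Aim 3 part is therefore conditional; the Aim 2 part is not.
- **Drop-out is already allowed for**: "Allowing for 20% drop out during follow-up, 38 participants will be recruited". That protects the number of participants in Aim 1, but it does not address who remains in Aims 2 and 3.
- **A mid-study change could mix time scales.** By 18 August 2023, 14 women had started. C1 answers counted from day 0 in some women and day 7 in others would not be comparable. Recording a calendar date, and back-dating the earlier answers, meets this.

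The loss may also be small, and the article already concedes that the sample is small for the number of variables.

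**Conclusion.** The concern holds for Aim 2, and for Aim 3 where the day-0 BIST is analysed. The stated schedule makes these cross-sectional comparisons depend on a later survey response, chiefly for naturally cycling women. No stated figure is wrong and the primary sample size is unaffected.

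The size is unknown. The illustrated fall in power, from 80% to between 77% and 66%, rests on assumed early losses, an assumed f of 0.6 and equal groups. Selective non-response is plausible but undocumented. The change is worth making because the groups are very small, the loss is avoidable and the remedy is cheap. The timing of the two one-off questions is secondary.

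**What to change.** 1. At the initial assessment, record contraceptive type (OCP or IUD) and, for naturally cycling women, the calendar date of the last period. Mark this in Table 2.
2. State that Aim 2 includes every woman with a saliva result, and Aim 3 every woman with a day-0 BIST where that is the outcome, regardless of later response.
3. Keep the full LEAF-Q weekly from day 7 for Aim 4.
4. For women already enrolled, back-date the day-7 C1 answer to the injury date so that all grouping is on one time scale. Recruitment is within three days of injury, so the shift is about 7 to 10 days. Because C1 has week-wide categories, the result is approximate.
5. Secondary: collect the prior-concussion count and sport status at the initial assessment too, or re-present them at the next link if missed. The ED check of concussion history already covers part of this.

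The cost is one or two extra minutes at the initial assessment and a small edit to Table 2. With 14 of 38 started by 18 August 2023, the change would have applied to the remaining 24 from that date.
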